### Blinding

We will use the non-penetrating Park-sham apparatus as a comparator. The same guide tube from the Park-sham needle will be used in both groups and, simultaneously, a fake noise from an identical electrical stimulator will be generated to maintain blinding during the procedures (see the section, Sham electroacupuncture). In addition, outcome assessors will be blinded, who are different from the study coordinators, TKM doctors performing the acupuncture procedures, and statistician. Unblinding before completing the study will only be allowed in cases of medical emergencies induced by serious adverse events (SAEs). At the end of the study, patients and outcome assessors, respectively, should try to deduce which group they thought to belong to. These answers will be used to calculate the new blinding index (BI) to evaluate success or failure of blinding [14].

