#### Blinding index

Patient and assessor blinding will be evaluated separately with a new BI [14]. They are going to be asked which group they think they belong to and select one of the following answers: verum EA group, sham EA group, or unknown. The index score varies from 1 (complete lack of blinding), 0 (consistent with perfect blinding), or − 1 (guessed they were in the opposite group). This will be assessed at the end of study.

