### Power calculation

The primary endpoint is the mean difference of the VAS scores for poststroke shoulder pain between the baseline and the endpoint. The null hypothesis is that μ_v_ = μ_s_*,* while the alternative hypothesis is *μ*_*v*_ ≠ *μ*_*s*_, where *μ* is the mean difference and *v* and *s* denotes the verum or sham EA group, respectively. A previous study to compare the effectiveness of acupuncture therapy using non-acupoint sham acupuncture on poststroke shoulder pain [29] showed the reductions of VAS scores with means ± standard deviations of 3.52 ± 2.67 in the intervention group and 1.38 ± 2.43 in control group, respectively. Using a two-sided test, under the assumptions of an of 0.05 and (1-β) of 0.8, a sample size of 24 per group has been calculated. Considering a 20% of dropout rate, a total of 60 participants will be enrolled in the trial (30 per group).

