### Statistical analysis

A full analysis set is defined as a group of participants who receive 7 or more verum or sham EA sessions with an evaluation of the primary outcome at the endpoint, while a per protocol set is a subset of participants who complete all verum or sham EA sessions as planned in the protocol. We are going to statistically analyze the obtained data, primarily on the full analysis set, as well as, on the per protocol set for the efficacy analysis. Missing values will be imputed by the method of last observation carried forward in the full analysis set.

Demographic information will be tested with a two-sample t-test or Wilcoxon rank sum test for continuous variables and chi-squared test or Fisher’s exact test for categorical variables. When statistically significant differences between groups are found in demographic information, especially age and sex, those will be used as covariates for effectiveness analysis.

Primary and secondary variables will be summarized using the mean ± standard deviation and tested by two-sample t-test or Wilcoxon rank sum test depending on normality of the distribution. If concomitant treatments are significantly different between groups, intergroup effect will be tested by an analysis of covariance with the information of concomitant treatments adjusted. For the intragroup effect, the results of the VAS scores will be tested by paired t-test or Wilcoxon signed rank test. The significance level will be set at 0.05 (two-sided). Statistical analyses will be performed using SAS® 9.4 software (SAS Institute Inc., North Carolina, USA) by an independent statistician ([name]).

The number of adverse events will be presented with a 95% confidence interval on a safety set defined as a subset of participants who receive at least one verum or sham treatment. A chi-squared test or Fisher’s exact test will be carried out to compare the significant differences between groups.

The results of the blinding assessment will be presented as the number of participants per group assignment with the participants’ deductions of their group assignment in a 2 × 3 table. We will consider blinding to be successful in this study if the calculated confidence interval of the new BI includes zero, following the previous study [14].

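### Calling blinding successful whenever the confidence interval of the blinding index includes zero treats failure to detect unblinding, with 24 to 30 answers per arm, as success

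*Protocol article*

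**What the plan says.** The Blinding section says that patients and outcome assessors will guess the allocation at the end of the study, and that the answers serve "to calculate the new blinding index (BI) to evaluate success or failure of blinding". The Blinding index section adds: "Patient and assessor blinding will be evaluated separately with a new BI". The permitted answers are "verum EA group, sham EA group, or unknown", and on timing: "This will be assessed at the end of study". The scale is described so: "The index score varies from 1 (complete lack of blinding), 0 (consistent with perfect blinding), or − 1", the last value standing for guesses of the opposite group.

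The Statistical analysis section plans a 2 × 3 table of assigned group by guess and then sets the criterion: "We will consider blinding to be successful in this study if the calculated confidence interval of the new BI includes zero". It cites a previous study for this. It gives no margin and no limit on the width of the interval.

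The number of answers follows from the Power calculation, which rests on the VAS alone: 24 per group are needed, and after allowance for 20% dropout "a total of 60 participants will be enrolled in the trial (30 per group").

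**The concern.** The criterion is a test of the null hypothesis that the index is zero, with non-rejection read as success. Non-rejection can mean good blinding or too few answers, and the rule cannot tell these apart. In general, the fewer the answers, the wider the interval and the easier the pass. That is the wrong incentive for a check on trial quality.

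It matters here because the primary outcome is rated by the patient, and the two procedures feel different in principle. Verum needles are inserted 10–15 mm, de qi is elicited and current is delivered. Sham needles do not penetrate and conduct no current. A statement that blinding succeeded would be used to defend the VAS result.

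The rule is also two-sided. The Sham electroacupuncture section aims for sham patients to believe they are receiving the real treatment. If that works well, the sham-arm index is negative, and its interval may lie wholly below zero and so fail to include it.

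**Working it through.** **Inputs from the protocol article.** 30 enrolled per group, 24 per group after 20% dropout, three answer categories, index from −1 to 1, success if the interval includes zero.

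**Assumptions, not stated for the index.** It is calculated per arm as BI = p(correct) − p(wrong), which fits the scale and the three answers. The variance is Wald: [p(correct) + p(wrong) − BI²]/n. The interval is 95% two-sided. The share answering 'unknown' is 0%, 20% or 40%.

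**1. The plan's own figure.** VAS reductions of 3.52 ± 2.67 and 1.38 ± 2.43 give a difference of 2.14 and a pooled SD of √[(2.67² + 2.43²)/2] = 2.553. The normal formula gives 2 × (1.96 + 0.842)² × 2.553²/2.14² ≈ 22.3, so 23. The t-based solution is 23.34, so 24, and 24/0.8 = 30. The stated sizes reproduce, but they say nothing about precision of the blinding index.

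**2. Precision at BI = 0.** The half-width is 1.96 × √[(1 − u)/n], where u is the share answering 'unknown'.

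| n per arm | u = 0% | u = 20% | u = 40% |
|---|---|---|---|
| 30 | 0.36 | 0.32 | 0.28 |
| 24 | 0.40 | 0.36 | 0.31 |

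**3. What passes.**
- 20 correct and 10 wrong of 30: BI = 10/30 = 0.333; variance = (1 − 0.111)/30 = 0.0296; half-width = 0.337; interval −0.004 to 0.671. Passes.
- 21 and 9 of 30: BI = 0.40, interval 0.07 to 0.73. Does not pass.
- 16 and 8 of 24: BI = 0.333, half-width 0.377, interval −0.04 to 0.71. Passes.
- 17 and 7 of 24: BI = 0.417, interval 0.05 to 0.78. Does not pass.
- 16 correct, 8 wrong and 6 'unknown' of 30: BI = 0.27, interval −0.04 to 0.57. Passes.

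With no 'unknown' answers, the attainable limit is therefore two thirds correct at both sizes.

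**4. Probability that one arm passes.** Exact trinomial enumeration, with p(correct) = (1 − u + BI)/2:

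| True BI | n | u = 0% | u = 20% | u = 40% |
|---|---|---|---|---|
| 0.2 | 30 | 82% | 73% | 67% |
| 0.2 | 24 | 81% | 77% | 72% |
| 0.3 | 30 | 64% | 49% | 37% |
| 0.3 | 24 | 64% | 57% | 46% |
| 0.4 | 30 | 41% | 24% | 11% |
| 0.4 | 24 | 44% | 33% | 19% |

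With no 'unknown' answers, 24 and 30 per arm barely differ because few values are attainable. The dependence on n shows in the other columns, and at n = 100 a true index of 0.3 passes only 13% (u = 0%) or 7% (u = 20%) of the time. With a 90% interval at n = 30, a true index of 0.3 passes in 49%, 39% or 26%.

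**5. The other direction.** By symmetry, a true index of −0.4 at n = 30 gives an interval that misses zero in 100% minus the corresponding row above: 59%, 76% or 89% of trials.

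**6. Could the trial support a positive verdict?** To have the whole 95% interval inside ±m with 80% probability at true BI = 0, n ≈ (1.96 + 1.282)² × (1 − u)/m². For m = 0.3 this is 71 to 117 per arm; for m = 0.2, 158 to 263 (u = 40% to 0%). Both margins are illustrative; the article gives none.

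**The case against.** **The planned data are sound.** The table of guesses by arm, the separate evaluation of patients and assessors, and an interval are all in the plan, so a reader could recompute a per-arm index whatever label is attached. That stands, and it limits the harm. It does not repair the label, which is a definite statement of what the trial will conclude.

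**The rule follows a cited study.** That source is not available here, so its interval level and form cannot be checked. A citation does not make non-detection evidence of blinding at this sample size.

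**The figures depend on assumptions.** True. 64% is the top of the range for a true index of 0.3. If the verdict required both arms to pass, each with a true index of 0.3, it would be about 41%, 24% or 13% at 30 per arm (the squares of the single-arm figures). The logical fault is the same in every case.

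**Two stronger readings.** A reader might infer that the protocol claims proof of blinding. It says only that blinding will be considered successful. A reader might also infer that a clearly negative sham-arm index will be scored as failure. The article does not say so: it states when success is declared, and it describes −1 separately from complete lack of blinding. Because the Blinding section speaks of success or failure, it is fair to say that the rule would withhold success in that case, and no more.

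**Conclusion.** The point holds. As written, the rule treats an undetected departure from zero as successful blinding. Under the assumptions shown (per-arm index, Wald variance, 95% interval), an arm with a true index of 0.3 passes in about 37% to 64% of trials at 30 per arm and 46% to 64% at 24 per arm, depending on the share of 'unknown' answers. The rule would also withhold success from a sham arm with a true index of −0.4 in 59% to 89% of trials at 30 per arm, although such an arm meets the sham's stated aim.

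Nothing here shows that blinding will be poor, and the VAS test, the sample size and the analysis sets do not depend on the rule. A reader might infer that the primary analysis is compromised; the article does not support that. What is affected is the claim the trial may make about blinding of a patient-rated outcome. Severity is moderate to minor.

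**What to change.** Delete the sentence that equates an interval including zero with success. In its place:

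- Report the index with its 95% confidence interval separately for each arm, for patients and for assessors, and state the variance formula.
- Interpret the patients' two arms jointly. For example, a positive verum index with a negative sham index means that both arms believed they had real electroacupuncture, which differs from both arms guessing correctly.
- State that unblinding up to the upper confidence limit cannot be excluded, and that at an index of zero the expected half-width is about 0.28–0.36 with 30 answers per arm and 0.31–0.40 with 24.

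The cost is a few lines in the analysis section and no extra patients or data. The downside is that the trial can no longer declare blinding successful by this rule. A margin-based verdict is not a realistic substitute, since even the illustrative ±0.3 would need 71 to 117 per arm.

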## Discussion

This is the study protocol of a double-center, randomized, sham-controlled, patient- and assessor-blinded parallel trial to explore the effectiveness and safety of EA therapy, compared to a sham EA therapy, for poststroke shoulder pain. The eligible patients will be recruited in 2 TKM hospitals in the Republic of Korea.

Acupuncture therapies have been clinically studied, and based on the evidence from those studies, clinical practice guidelines have been published for general rehabilitation [30] or specific conditions of stroke survivors [31, 32]. In a systematic review, acupuncture combined with rehabilitation therapy showed therapeutic effect for shoulder pain occurring after a stroke [9]; however, clinical evidence for EA therapy for the same condition is generally lacking [9, 10]. For this reason, we have chosen to use EA intervention combined with the usual therapy for poststroke shoulder pain. In addition, previous EA studies do not compare the intervention with validated sham devices [33, 34], which made us consider the necessity of a sham-controlled trial.

There is no clear evidence for the most suitable time to begin treating shoulder pain after a stroke occurs. However, approximately 72% of individuals with HSP are estimated to develop symptoms 2 weeks after the onset of stroke [3]. We will recruit patients who are in this poststroke phase to show overall effectiveness.

A literature review addressed the selected acupoints (LI4, LI15, TE14, SI9, SI11, and GB21) that have been proposed to treat general shoulder pain, which are based on the standards of TKM [35]. Additionally, most acupoints are anatomically located around the muscles involving shoulder movement. Therefore, we expect EA treatment on these acupoints to be beneficial for poststroke shoulder pain, similar to the results presented in a systematic review on the stimulation of Ashi points for general shoulder pain [36].

## Abbreviations

BI: blinding index
BTX-A: botulinum toxin A
CT: computed tomography
EA: electroacupuncture
FMA-UE: Fugl-Meyer assessment upper extremity
HSP: hemiplegic shoulder pain
K-BDI: Korean version of Beck depression inventory
K-MBI: Korean version of modified Barthel index
MAS: modified Ashworth scale
MMT: manual muscle test
MRI: magnetic resonance imaging
PROM: passive range of motion
PRS: pain rating scale
RCT: randomized controlled trial
SAE: serious adverse event
SPIRIT: standard protocol items: recommendations for interventional trials
STRICTA: revised standards for reporting interventions in clinical trials of acupuncture
TKM: traditional Korean medicine
VAS: visual analog scale
